### 2.8 Care for control group

The control group will participate in a six-month program, which is similar to the intervention group in structure but excludes the harmonica sessions. This group will undergo the same educational and rehabilitation training sessions as the intervention group. The specific activities will be detailed in Table 1.

#### 2.8.1 Supervision and guidance for control group

After randomization, control group participants will be added to a dedicated WeChat group comprising participants, their family members (optional), a home-training recorder and supervisor, and a rehabilitation instructor. The same recording methods and daily prompts will be applied as in the intervention group. The home-training supervisor will review uploaded videos, monitor adherence, send daily reminders, and track training completion. The rehabilitation instructor will conduct real-time video assessments to ensure proper adherence to the training protocols.

### 2.9 Outcomes

Primary and secondary outcomes will be assessed at four key intervals: baseline (T0), 1 month (T1), 3 months (T2), and 6 months (T3) post-baseline, as shown in Table 2. Secondary outcomes related to “adherence and satisfaction” will be measured only at T1, T2, and T3.

**Table 2 T2:** Assessment of primary and secondary outcomes.

**Outcomes**	**Time points**	**Measurement tools and methods**
**Primary outcome**		
Lung function	T0, T1, T2, and T3	Forced expiratory volume in one second percent of predicted (FEV_1_%) 48 h after discontinuing inhaled bronchodilators
**Secondary outcome**		
Inspiratory muscle strength	T0, T1, T2, and T3	Maximum inspiratory pressure (PImax)
Expiratory muscle strength	T0, T1, T2, and T3	Maximum expiratory pressure (PEmax)
Exercise capacity	T0, T1, T2, and T3	6-min Walking Test (6MWT)
Fatigue	T0, T1, T2, and T3	Checklist Individual Strength-Fatigue (CIS-Fatigue) Functional Assessment of Chronic Illness Therapy-Fatigue (FACIT-F) Scales
Breathlessness level	T0, T1, T2, and T3	Modified Medical Research Council (mMRC) Dyspnea Scale
Clinical symptoms	T0, T1, T2, and T3	COPD Assessment Test (CAT)
Clinical control	T0, T1, T2, and T3	COPD Control Questionnaire (CCQ)
Mental health	T0, T1, T2, and T3	Hospital Anxiety and Depression Scale (HADS)
Self-efficacy	T0, T1, T2, and T3	Chronic Obstructive Pulmonary Disease Self-Efficacy Scale (CSES)
Quality of life	T0, T1, T2, and T3	St. George's Respiratory Questionnaire (SGRQ)
Social support status	T0, T1, T2, and T3	Multidimensional Scale of Perceived Social Support (MSPSS)
Adherence and satisfaction	T1, T2, and T3	Recording and self-designed questionnaire

COPD, Chronic Obstructive Pulmonary Disease; T0, baseline; T1, 1 month post-baseline; T2, 3 months post-baseline; T3, 6 months post-baseline.

#### 2.9.1 Primary outcomes

The primary outcome of this study is the change in lung function, measured as FEV_1_% 48 h after discontinuing inhaled bronchodilators. Measurements will be obtained using the portable X1 spirometer (serial no. X1231100300024) from Saikemed (Xiamen) Medical Equipment Co., Ltd. Predicted FEV_1_ values will be calculated based on the “Compilation of Normal Lung Function Values Across China” (Mu Kuijin & Liu Shiwuan, eds.): for males, FEV_1_ = −1.087 – 0.029 × A + 0.033 × H; for females, FEV_1_ = −0.753 – 0.022 × A + 0.026 × H, where A is age (years) and H is height (cm) (18). A clinically significant change is defined as a ≥4% improvement in FEV_1_%, a recognized MCID in COPD research (16). COPD severity will be classified according to the ATS/ERS criteria (2005/2019) based on post-bronchodilator FEV_1_%: mild (≥70%), moderate (60–69%), moderate-to-severe (50–59%), severe (35–49%), and very severe (< 35%) (19).

#### 2.9.2 Secondary outcomes

Secondary outcomes will encompass changes in respiratory muscle strength, exercise capacity, fatigue, breathlessness, clinical symptoms, clinical control, mental health, self-efficacy, quality of life, social support, adherence and satisfaction. Each outcome will be measured using validated tools accordingly to ensure reliable and actionable insights.

##### 2.9.2.1 Inspiratory and expiratory muscle strength

Inspiratory and expiratory muscle strength will be measured as PImax (maximum inspiratory pressure) and PEmax (maximum expiratory pressure) using the X1 spirometer (serial no. X1231100300024).

##### 2.9.2.2 Exercise capacity

The 6-min walk test (6MWT) is a validated measure of exercise capacity in COPD patients, demonstrates reliable performance in the Chinese population and correlates with disease severity and mortality (20). Participants will complete a 6-min walk along a standardized flat corridor, with total distance walked serving as the primary outcome metric. Heart rate and perceived exertion (Borg scale) will be assessed pre- and post-test to evaluate exercise intensity and physiological recovery. Predicted 6MWD (meters) will be calculated using Enright and Sherrill's formulas based on body mass index (BMI) and age: for males, 6MWD = 1,140 – 5.61 × BMI – 6.94 × age; for females, 6MWD = 1,017 - 6.24 × BMI – 5.83 × age. These values will provide a reference for interpreting the actual distance walked (21).

##### 2.9.2.3 Fatigue

Fatigue will be measured using the Chinese version of the Checklist Individual Strength-Fatigue (CIS-Fatigue; Cronbach's alpha of 0.88) and Functional Assessment of Chronic Illness Therapy-Fatigue (FACIT-F; Cronbach's alpha of 0.90) scales. Both scales are validated in Chinese populations and are widely used in assessing fatigue in chronic illness (22, 23). The CIS-Fatigue, a 20-item subscale of the Checklist Individual Strength, employs a 7-point Likert scale with total scores ranging from 8 to 56, where scores < 26, 27–35, and >36 represent normal, mild, and severe fatigue, respectively. The FACIT-F, a 13-item self-reported scale rated on a 5-point Likert scale (“not at all” to “very much”), measures fatigue-related tiredness, weakness, and activity limitations over the preceding seven days. Higher scores on both scales indicate greater fatigue (24).

##### 2.9.2.4 Breathlessness level

The mMRC Dyspnea Scale, with a Cronbach's alpha of 0.82 in China, will assess breathlessness severity on a 0–4 scale. A score of 0 indicates no breathlessness, while 1 represents breathlessness when hurrying or walking uphill. Scores of 2 and 3 correspond to slower walking or stopping for breath after 100 meters or a few minutes on level ground, respectively. A score of 4 indicates breathlessness when dressing or an inability to leave the house. This scale is commonly used in Chinese COPD research and clinical practice, showing strong correlations with pulmonary function and quality of life (25).

##### 2.9.2.5 Clinical symptoms

Clinical symptoms will be evaluated using the Chinese version of the COPD Assessment Test (CAT; Cronbach's alpha of 0.805), a 5-point scale with 8 items assessing cough, sputum, dyspnea, chest tightness, confidence, activity, sleep, and energy. Scores range from 0 to 40: 0–10 (mild), 11–20 (moderate), 21–30 (severe), and 31–40 (very severe) impact. The CAT, validated in the Chinese COPD population, is sensitive to clinical changes and strongly correlates with health-related quality of life (26).

##### 2.9.2.6 Clinical control

Clinical control will be assessed using the Chinese version of the Clinical COPD Questionnaire (CCQ; Cronbach's alpha of 0.90) (27), a 10-item tool evaluating symptoms, function, and mental state. Items are scored on a 7-point scale (0 = no impairment, 6 = most severe impairment), with higher scores indicating poorer disease control. It is validated in Chinese COPD patients and correlates with clinical outcomes and quality of life (28).

##### 2.9.2.7 Mental health

Anxiety and depression will be assessed using the Chinese version of the Hospital Anxiety and Depression Scale (HADS; Cronbach's alpha of 0.78–0.93) (29), a 4-point scale (0–3) tool with 14 items, divided into two subscales: anxiety (HADS-Anxiety 7 items) and depression (HADS-Depression, 7 items). Each subscale is scored from 0 to 21, with categories: 0–7 (normal), 8–10 (mild), 11–14 (moderate), and 15–21 (severe). The HADS is widely validated in Chinese COPD clinical settings as a reliable measure of psychological distress (30).

##### 2.9.2.8 Self-efficacy

Self-efficacy will be measured using the Chinese version of the Chronic Obstructive Pulmonary Disease Self-Efficacy Scale (CSES; Cronbach's alpha > 0.80), which is validated for use in Chinese populations (31). This 20-item, 10-point scale (0–10) assesses symptom management, physical activity, and psychological coping, with total scores ranging from 0 to 200. Higher scores indicate greater self-efficacy in managing COPD (32).

##### 2.9.2.9 Quality of life

The Chinese version of the St. George's Respiratory Questionnaire (SGRQ; Cronbach's alpha of 0.97) will be used to assess subjective quality of life (33). It has been validated for use in COPD patients in China and is an essential tool for capturing the multidimensional impact of COPD on patients' lives, including respiratory symptoms (e.g., cough, sputum, dyspnea), activity limitations (e.g., walking, sports, chores), and disease impacts (e.g., walking, sports, chores). Scores, ranging from 0 (no impairment) to 100 (worst health), are calculated as a weighted average of the individual item scores, with higher scores indicating a greater disease impact (34).

##### 2.9.2.10 Social support

The Chinese version of the Multidimensional Scale of Perceived Social Support (MSPSS; Cronbach's alpha of 0.91) (35) will assess perceived social support from family, friends, and significant others using a 12-item, 7-point Likert scale (1–7). Subscale scores range from 4 to 28, and total scores from 12 to 84, with higher scores indicating greater perceived support. It has shown reliability in the Chinese population and is an effective tool for assessing social support in COPD patients (36).

##### 2.9.2.11 Adherence and satisfaction

Adherence and satisfaction will be assessed at T1, T2, and T3. Adherence will be quantified by recording attendance and exercise completion. Satisfaction will be assessed using a study-specific questionnaire designed to comprehensively capture participants' perceptions.

### 2.10 Statistical analysis

Data will be collected using a dual-entry and verification process, incorporating range checks, logic tests, and source document validation to ensure data integrity (37). All analyses will be conducted with R software version 4.4.0. The primary analysis will follow the intention-to-treat principle (ITT), including all randomized participants in their assigned groups (38). Baseline characteristics will be summarized using descriptive statistics, with continuous variables compared using independent *t*-tests and categorical variables using chi-square tests between the harmonica-integrated PR group and the standard PR care group. Primary and secondary outcomes will be analyzed using mixed-effects models to account for the repeated measures design (39). Sensitivity analyses will include per-protocol analyses focusing on participants who fully adhered to the intervention. Effect sizes and 95% confidence intervals will be reported alongside *p*-values. All statistical tests will be two-tailed, with significance set at *p* < 0.05. Subgroup analyses will be conducted based on pre-specified baseline characteristics as necessary. Cohen's D will be used as the effect size metric, with common thresholds (small: 0.2, medium: 0.5, large: 0.8) (40).

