### 2.3 Eligibility and sample size

Eligible patients must have a clinical diagnosis of COPD and a post-bronchodilator forced expiratory volume in one second (FEV_1_) to forced vital capacity (FVC) ratio of < 70%. Exclusion criteria include recent COPD exacerbations (within 6 weeks), resting oxygen saturation (SpO_2_) below 88% on room air or inadequate oxygenation despite supplementation; as well as severe dyspnea with Modified Medical Research Council (mMRC) grade 4, recent myocardial infarction, unstable angina, severe arrhythmias (e.g., ventricular arrhythmias or rapid atrial fibrillation), or pulmonary hypertension with right heart failure. Additional exclusions include comorbidities affecting physical activity (e.g., neurological disorders, cancer, significant musculoskeletal issues), cognitive impairments, and inability to communicate in Chinese. Furthermore, those with prior participation in PR within 6 months, or regular experience playing harmonica or similar wind instruments, are excluded to ensure baseline equivalence, minimize learning and behavioral biases, and avoid psychological effects, thereby enhancing the validity and reliability of the study outcomes.

Based on an anticipated minimum clinically important difference (MCID) of a 4% increase in percent predicted FEV_1_ (FEV_1_%) and a standard deviation of 10% (16), each group will require 99 participants to achieve 80% power at a 0.05 two-tailed significance level. Considering a 20% dropout rate, the study plans to enroll 248 patients (124 per group) (17).

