#### 2.7.4 Tele-supervision and guidance for intervention group

Upon randomization, a WeChat group will be established for each intervention cohort, including participants themselves, their family members (if they choose), a home-training supervisor and recorder, a rehabilitation instructor, and a harmonica instructor. For participants with limited device familiarity or access, one-on-one personalized WeChat training will be conducted at baseline, including video tutorials, content uploads, and interaction with PR staff. Family members will be trained if needed to assist with remote monitoring.

Participants will upload daily videos of their training and harmonica playing, report training duration, and complete rehabilitation training diaries documenting exercise and harmonica practice times. The supervisor and recorder will independently review the videos to verify adherence, and discrepancies will be resolved through double-checking the video recordings. Additionally, the supervisor and recorder will send daily reminders, track attendance, and note any absences. Rehabilitation and harmonica instructors will conduct real-time video assessments of participants' techniques, providing immediate feedback, personalized guidance, and addressing participant queries.

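### The sensitivity analysis named in section 2.10 keeps only full adherers, a requirement that reads as heavier in the harmonica arm, so it cannot test the robustness of the intention-to-treat result

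*Protocol article*

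**What the plan says.** Section 2.10 bases the primary analysis on all randomised participants in their assigned groups, using mixed-effects models. The only sensitivity analysis it names is this: "Sensitivity analyses will include per-protocol analyses focusing on participants who fully adhered to the intervention". It does not say which components count or what level is full. Section 2.9.2.11 says only that adherence is recorded as attendance and completion of exercises.

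The two programmes differ in what there is to adhere to. Under Table 1 and section 2.7.2, the training that both arms receive is done at home five days a week for six months. Table 1 and section 2.7.3 add, for the harmonica arm only, 30 minutes of unbroken practice and three lessons. Section 2.8 leaves these out of the control programme. Table 1 sets harmonica practice at five days a week, whereas section 2.7.3 makes it daily.

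Section 2.3 gives the planning figures: an "anticipated minimum clinically important difference (MCID) of a 4% increase in percent predicted FEV"1, "a standard deviation of 10" (per cent), and "each group will require 99 participants to achieve 80% power at a 0.05 two-tailed significance level". It continues: "Considering a 20% dropout rate, the study plans to enroll 248 patients (124 per group").

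**The concern.** A sensitivity analysis of an ITT result should keep the same question and vary an assumption behind the answer. Restricting to full adherers changes the question, to the effect among people who complied, and gives up the comparability that randomisation provides. Those who comply fully are likely to differ from the rest in motivation, severity and health.

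If both arms faced the same requirement, similar selection on each side might partly cancel. Here it is unlikely to, because the harmonica arm has more to complete. The discussion section itself acknowledges the extra time demanded of that arm. If fewer people pass the heavier test and adherence goes with better lung function, those left in the harmonica arm are the more favourably selected group.

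At stake is interpretation. A per-protocol difference inflated in this way, reported as a sensitivity analysis, would look like support for the ITT result without being a check on it.

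**Working it through.** **1. The plan's own figure.** Inputs from section 2.3: difference 4, SD 10, two-sided 0.05, power 80%, dropout 20%.

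n per arm = 2 × (1.960 + 0.842)² × 10² / 4² = 98.1, rounded up to 99. With dropout, 99 / 0.80 = 123.75, rounded up to 124 per arm, 248 in total. The stated figures reproduce.

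**2. What full adherence covers in each arm, taking six months as 26 weeks.**

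| Component | Control | Harmonica |
|---|---|---|
| Home training days, 26 × 5 | 130 | 130 |
| Harmonica practice, Table 1, 26 × 5 | 0 | 130 |
| Harmonica practice, section 2.7.3, 26 × 7 | 0 | 182 |
| Harmonica lessons | 0 | 3 |

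Home tasks come to 130 in the control arm, against 260 or 312 in the harmonica arm, depending on which frequency holds.

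**3. Bias from unequal selection, with no treatment effect.** Suppose adherence is a person-level trait correlated r with the outcome, and the top fraction f of an arm is kept. The kept group's mean then exceeds the arm's mean by SD × r × φ(z)/f, where z is the standard normal quantile at 1 − f.

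- f = 0.40: φ(0.253)/0.40 = 0.386/0.40 = 0.966
- f = 0.60: φ(−0.253)/0.60 = 0.386/0.60 = 0.644
- Shift in the difference = 10 × r × (0.966 − 0.644) = 3.22 × r

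This gives 0.32, 0.64 and 0.97 points for r = 0.1, 0.2 and 0.3. Keeping 50% v 60% gives 0.15 to 0.46 points; keeping 30% v 60% gives 0.52 to 1.55. The correlations and kept fractions are assumptions. Only the SD and the 4-point target come from the protocol.

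**4. How many might be kept.** The article gives no adherence rate, so only a range can be shown. Read literally (no missed task) and with tasks independent, the number kept out of 124 is 124 × p^130 for controls and 124 × p^260 for the harmonica arm (p^312 if practice is daily):

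| Completion per task, p | Control | Harmonica, 5 days | Harmonica, 7 days |
|---|---|---|---|
| 0.95 | 0.2 | 0.0 | 0.0 |
| 0.98 | 9.0 | 0.6 | 0.2 |
| 0.99 | 33.6 | 9.1 | 5.4 |
| 0.995 | 64.6 | 33.7 | 26.0 |
| 0.999 | 108.9 | 95.6 | 90.8 |

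Independence is doubtful, and it sits badly with step 3, which treats adherence as a personal trait. Letting people differ (beta-binomial over 130 days, mean completion 70% to 90%, intraclass correlation 0.2 to 0.4), between 1% and 48% complete every day. Under the same assumptions, a rule of at least 80% of days keeps 39% to 83%.

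**5. Precision of such a set.** The 95% half-width is 1.96 × 10 × √(1/n₁ + 1/n₂). With 50 v 50 kept it is 3.9 points and power for 4 points is 0.52. With 34 v 34 the figures are 4.8 and 0.38.

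**The case against.** The strongest reply is that this is one loose phrase about a secondary analysis in a condensed article. The per-protocol definition may sit in an unseen analysis plan. The adherence measure in section 2.9.2.11 could be applied alike in both arms. The direction of bias is also not certain: the introduction expects the harmonica to make training more engaging, and if that arm kept the larger share, the sign in step 3 would reverse.

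Much of this stands as a limit on size and certainty. It does not remove the point, because the article itself chose both full adherence as the rule and sensitivity as the label.

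Three stronger readings are tempting, and the documents do not support them.

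- *The per-protocol set will be almost empty.* This holds only for a literal rule with per-task completion of about 0.98 or lower, or with little variation between people. Step 4 runs from about 0% to 88% of controls and from 0% to 77% of the harmonica arm.
- *Control adherence is checked less strictly.* Section 2.7.4 says "The supervisor and recorder will independently review the videos to verify adherence", while section 2.8.1 says "The home-training supervisor will review uploaded videos, monitor adherence, send daily reminders, and track training completion", which might suggest one reviewer instead of two. But section 2.8.1 also lists a recorder in the control group and states that recording is done in the same way as in the intervention group.
- *Dropout goes unexamined.* Section 2.3 allows for 20% dropout, and the discussion expects more of it in severe disease. The list of sensitivity analyses is worded as open, however, and missing-data analyses are commonly left to the analysis plan. Their absence here is no finding.

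**Conclusion.** The point holds in limited form. The named analysis conditions on behaviour after randomisation and, if harmonica practice counts towards adherence, on a heavier requirement in one arm. Its contrast can be biased, probably towards harmonica. The illustration of 0.3 to 1.0 points is up to about a quarter of the 4-point target; it rests on 40% v 60% kept and a positive adherence-outcome correlation of 0.1 to 0.3. Whatever the size of the bias, the analysis answers a different question and cannot show that the ITT result is robust. The retained number cannot be determined from the article. The primary ITT analysis and the sample size are unaffected, so this is a worthwhile, inexpensive improvement and not a threat to the trial's main conclusion.

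**What to change.** 1. Call the per-protocol analysis supplementary, and do not offer it as a sensitivity analysis of the ITT result.
2. Estimate the effect of adherence in all randomised participants with randomisation as the instrument. Preferably use the proportion of prescribed harmonica sessions completed: a single cut-off would assume no effect on anyone below it. State the exclusion assumption, that allocation affects FEV1% only through the sessions completed.
3. If a per-protocol set is kept, define it by one threshold on the shared training components, set before outcomes are seen and applied identically in both arms.
4. Reconcile the practice frequency in Table 1 with that in section 2.7.3, so that prescribed harmonica sessions can be counted.

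The cost is wording and modest programming on adherence data already being collected, plus wider intervals. In its simplest form, the instrumental estimate divides the ITT difference and its interval by mean completion in the harmonica arm. With 99 per arm the ITT half-width is 1.96 × 10 × √(2/99) = 2.8 points. At an assumed mean completion of 90% or 70% it becomes 2.79/0.9 = 3.1 or 2.79/0.7 = 4.0, on the scale of the effect at full completion.

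As a recommendation only, since the analysis plan may already contain it: let the sensitivity analysis of the ITT result vary the missing-data assumption, for example by delta-adjusted imputation.

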## 3 Discussion

By leveraging the respiratory benefits of harmonica playing—which simulates respiratory training and incorporates the advantages of music therapy—along with the convenience of home-based training and the instant support of tele-supervision, this study aims to evaluate the effectiveness of a harmonica-integrated, tele-supervised home-based PR program. This innovative approach may offer an accessible, affordable, and enjoyable non-pharmacological treatment option for patients with COPD.

With a robust sample size of 248 participants, a six-month intervention, standardized protocols, and comprehensive outcome measures, the study enhances statistical power, generalizability, and long-term assessment (41, 42). Key design features include a partially blinded methodology, where care providers, outcome assessors, and data analysts are unaware of group assignments, minimizing bias and ensuring objective evaluation (43). The home-based approach improves accessibility for remote or mobility-limited patients, reduces travel and costs, and may lower infection risks compared to clinic settings (44, 45). Tele-supervision involves roles such as home-training recorder, supervisor, and instructors, providing real-time guidance and technique correction. Communication via WeChat fosters a supportive community, while video recordings ensure objective adherence data (46). Harmonica training progresses from basic music theory and breathing techniques to advanced playing skills, promoting mastery and enjoyment. Concurrently, comprehensive PR sessions include breathing exercises (e.g., pursed-lip, diaphragmatic) and physical activities (e.g., air cycling, hip bridge, resistance band stretching) to enhance respiratory and overall muscle function (41, 47). Regular technical assessments and introductory guidance support effective home-based training.

This intervention offers scalable advantages over traditional rehabilitation methods by utilizing widely accessible technologies such as smartphones and WeChat, ensuring broad feasibility and seamless integration with existing healthcare systems (48). The harmonica's low cost and portability facilitate implementation in resource-limited settings without the need for specialized equipment. Tele-supervision and remote monitoring enhance efficiency, particularly in areas with limited rehabilitation services (49). To address unfamiliarity with equipment and limited access, one-on-one personalized WeChat training will provided at baseline, including video tutorials, content uploads and interacting with PR staff, with family members trained if needed to assist in remote monitoring.

Several limitations and challenges need attention and efforts to mitigate. The lack of participant blinding may introduce bias, especially for subjective outcomes. Emphasizing objective measures (e.g., lung function tests), blinded data analysts, strict quality control, and adherence to standardized protocols can partially mitigate this. Nonetheless, self-reported outcomes (e.g., satisfaction, quality of life, mental health) remain susceptible to expectation bias, requiring cautious interpretation of related outcomes. Self-selection bias, due to voluntary participation and the novelty of harmonica use, may also affect findings. Recording baseline characteristics and recruiting a diverse participant pool may mitigate this. While video evidence can reduce adherence bias, misreporting may still occur, enhanced supervision and daily confirmations could address this. The six-month duration may increase dropout rates, particularly among severe COPD patients. Regular follow-ups and motivational support may help, but additional recruitment may be necessary if dropout rates jeopardize statistical power. Furthermore, the single-center approach may limit generalizability, necessitating multi-center trials for broader applicability in the future. Failure to stratify participants by Global Initiative for Chronic Obstructive Lung Disease (GOLD) stage may lead to underrepresentation of certain stages, particularly GOLD 4, and potentially skew subgroup analyses. As treatment responses vary by stage, this lack of stratification could confound efficacy assessment. Given COPD's patient heterogeneity, not stratifying may result in inaccurate evaluations of intervention effectiveness among patients at different stages, affecting overall treatment judgment. Future study designs or RCTs should account for this. The absence of long-term follow-up will restrict the assessment of enduring effects, extended follow-up should be included in future trials. While time equivalence between the intervention and control groups is challenging, the primary activities (breathing and exercise training) ensure general time equivalence. Future analyses should consider additional time demands on the intervention group. While volume, frequency, and density are well-defined in our intervention, objective measures of intensity (e.g., breath pressure, mouth/tongue effort) remain unquantified. Inter-participant variability in technique may therefore introduce differences in actual training load, potentially impacting the findings and warranting cautious interpretation. Future research may explore device-based measures (e.g., breath pressure sensors, digital harmonicas) to better capture and standardize the intensity component of this intervention. Moreover the optimal duration and frequency for clinical outcomes are not yet established and should be explored in future trials.

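### Chance imbalance in baseline severity can be adjusted for in this trial with T0 FEV1%, but the Discussion leaves the remedy to future trials and section 2.10 states no adjustment

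*Protocol article*

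**What the plan says.** - **Randomisation (Protocol article, 2.5).** Allocation is 1:1 from a computer-generated list. No stratification factor is named.
- **Eligibility (2.3).** Entry needs an FEV1/FVC ratio below 70%. There is no upper or lower limit on FEV1%, although mMRC grade 4 and low resting oxygen saturation are excluded.
- **Discussion (3).** The article acknowledges that it does not stratify by GOLD stage and says that "this lack of stratification could confound efficacy assessment". The only remedy offered is that later designs should deal with it. The same section also expects that "The six-month duration may increase dropout rates, particularly among severe COPD patients".
- **Outcome (2.9, 2.9.1).** The primary outcome is the change in FEV1%, measured at T0, T1, T2 and T3.
- **Analysis (2.10).** "Primary and secondary outcomes will be analyzed using mixed-effects models to account for the repeated measures design". No model terms are listed. Baseline data have a stated role in the descriptive summary, in between-arm tests of baseline characteristics and in subgroup analyses, but none in the outcome model.
- **Sample size (2.3).** With a 4-point difference and an SD of 10, "each group will require 99 participants to achieve 80% power at a 0.05 two-tailed significance level". An allowance of 20% for dropout brings this to 124 per arm, or 248 in total.

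**The concern.** The Discussion names a threat to the primary result and presents it as something only another trial can address. For one part of that threat this is not so. Under unstratified randomisation the arms can differ by chance in mean baseline FEV1%. Baseline FEV1% is scheduled for every participant and should be the strongest available predictor of later FEV1%, so the model can correct for the difference.

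The form of the model matters. A four-visit mixed model can hold T0 as a response with the arms' T0 means left free. It then gives only the precision of a change score. It can instead hold the T0 means equal, as randomisation justifies, or use T0 as a covariate, and then it gives the precision of an analysis of covariance. The article does not say which is meant. At stake are some precision, and protection against a chance baseline difference that is not small beside the 4-point target.

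There is a lesser benefit as well. Dropout is expected to depend on severity, so an analysis that conditions on T0 FEV1% makes a missing-at-random assumption easier to defend.

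**Working it through.** **Inputs.** From 2.3: difference 4 points, SD 10, two-sided 0.05, power 80%, 99 per arm analysed, 124 per arm enrolled. From 2.9: visits T0 to T3. Not in the document, so assumed: the correlation r between T0 and follow-up FEV1%, taken as 0.5 to 0.9, and equal variance at all visits. Section 2.3 does not say whether the SD of 10 is for a single measurement or for change, so both readings are shown.

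**1. The plan's own figure.**
n per arm = 2 × (1.960 + 0.842)² × 10² / 4² = 98.1, rounded up to 99. Dropout: 99 / 0.80 = 123.75, rounded up to 124, or 248 in total. Both figures reproduce.
Power at 99 per arm: SE = 10 × √(2/99) = 1.421, and Φ(4/1.421 − 1.960) = 80.4% (80.0% with the noncentral t).

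**2. Variance with and without adjustment.** With visit variance σ², a change score has variance 2σ²(1 − r) and a baseline-adjusted value has σ²(1 − r²). The ratio is (1 + r)/2.

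**3. Four-visit model, effect at T3** (generalised least squares, compound symmetry, σ = 10, 99 per arm):

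| r | SE, T0 means free | SE, common T0 mean | Variance ratio |
|---|---|---|---|
| 0.5 | 1.42 | 1.23 | 0.75 |
| 0.7 | 1.10 | 1.02 | 0.85 |
| 0.8 | 0.90 | 0.85 | 0.90 |
| 0.9 | 0.64 | 0.62 | 0.95 |

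The model with free T0 means reproduces the change score. The model with a common T0 mean reproduces analysis of covariance. The reduction in variance is therefore 25%, 15%, 10% and 5%.

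**4. Power if 10 is the SD of change.** Adjusted SD = 10 × √((1 + r)/2), and power = Φ(4/(SD × √(2/99)) − 1.960):

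| r | Adjusted SD | Power at 99 per arm | n per arm for 80% |
|---|---|---|---|
| no adjustment | 10 | 80.4% | 99 |
| 0.5 | 8.66 | 90.1% | 74 |
| 0.7 | 9.22 | 86.3% | 84 |
| 0.8 | 9.49 | 84.3% | 89 |
| 0.9 | 9.75 | 82.3% | 94 |

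**5. Power if 10 is the SD of a single measurement.** A change score alone gives 80.4%, 95.3% and 99.4% at r = 0.5, 0.7 and 0.8. Adjustment gives 90.1%, 97.6% and 99.7%. On this reading there is little left to gain once r is high.

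**6. Chance imbalance.** With 124 per arm and a baseline SD of 10 (assumed), the difference in mean T0 FEV1% has SE 10 × √(2/124) = 1.27, so a 95% range of about ±2.5 points. A baseline difference d carries r × d into a comparison that ignores T0, −(1 − r) × d into a change-score comparison, and on average nothing into an adjusted one. At d = 2.5 and r = 0.8 these are 2.0, −0.5 and 0 points, against a target of 4.

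**The case against.** The strongest reply is that 2.10 is silent, and silence is not a decision. A journal article commonly leaves covariates and covariance structure to the full protocol or SAP, which are not shown. The primary outcome is defined as a change and T0 is one of the repeated measurements, so baseline is probably used already. If T0 is a response, the T0 difference is subtracted and a likelihood-based model already conditions on observed T0 values. If the T0 means are also constrained, nothing is lost at all.

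This stands as far as it goes. A reader might infer that the model omits baseline FEV1%; the document does not say so. A reader might also infer that power falls far below 80%. That would need both a larger SD, which the document does not give, and an analysis that ignores T0, which conflicts with the change outcome in 2.9.1. Nor can one conclude that an SD of 10 is credible only for change: the article gives no distribution of FEV1% for the patients it will enrol, and its exclusions and expected shortage of GOLD 4 may narrow the spread.

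A further reply is that the Discussion is largely about under-represented stages and treatment response that differs by stage. Adjusting for a baseline main effect cures neither. That is correct, and it limits the point to chance imbalance.

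What the reply does not meet is that the Discussion also refers to the overall efficacy result and offers this trial no analytic remedy, though one is at hand.

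**Conclusion.** The point holds as a cost-free improvement and a correction to the Discussion. It is not a demonstrated error in the model. Randomisation without stratification leaves chance imbalance in severity, not systematic confounding, and T0 FEV1% lets this trial adjust for it.

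Compared with a change-score or free-T0-mean analysis, the variance falls by about 15%, 10% and 5% at r = 0.7, 0.8 and 0.9. If 10 is the SD of change, power at 99 per arm goes from about 80% to 86%, 84% and 82%. These sizes rest on assumed correlations, equal variance across visits and, for the power figures, that reading of the SD. If the intended model already constrains the T0 means or includes T0 as a covariate, there is no loss and only the wording is needed.

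The stated 99 and 124 per arm assume no gain from adjustment and are not invalidated. Adjustment corrects the estimate for imbalance; it does not create balance, and it does not supply information on stages that are thinly recruited.

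**What to change.** - **Section 2.10, primary outcome.** Specify one of two models for FEV1%. Either use T0 to T3 as responses, with a T0 mean common to both arms and group-by-visit terms at the later visits; or use T1 to T3 as responses, with T0 FEV1% and its interaction with visit as covariates.
- **Section 2.10, secondary outcomes.** Adjust each outcome that is measured at T0 for its own T0 value. Adherence and satisfaction start at T1 and have none.
- **Discussion.** State that chance imbalance in baseline severity is adjusted for in the analysis. Keep the limitation on under-represented stages and stage-specific effects.

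The cost is wording only: no new data, visits or patients, and no change to the sample size. It should be fixed before outcome data by arm are seen.
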